### Patient and public involvement

In developing the current study protocol, we used feedback from a pilot study of 39 males (Centralised Institutional Review Board 2022/2452) to enhance participant engagement and streamline the study workflow. Feedback regarding willingness to participate, biosample provision and preferred timing of visits informed the planning of our study design and assessments. Additionally, participants in this study will receive their clinical blood and semen test results.

### Data collection and management

During the study visit (the only single timepoint visit), trained research staff will collect data on the sociodemographics and medical history of participants through interviews and medical record collection forms. They will also gather self-reported data on behavioural, lifestyle and environmental factor exposures from the past month using standardised questionnaires. The selection of the recall timeframe is based on the period specified in the validated questionnaires (table 1). Additionally, the staff will conduct anthropometric and body fat composition measurements, and collect blood, urine and semen samples from participants at the clinics in KKH. All data will be saved in a REDCap database. Access to this database is secured with a password, and only approved study team members can access the stored information.

**Table 1 T1:** Data and biosamples collected from both case and control participants

Male partners	Parameters
Sociodemographic, clinical, behavioural, lifestyle and environmental factors	Age, country of origin, length of time in Singapore if born overseas, ethnicity, education, occupation, monthly income, medical history, medication, family history, reproductive health history, male sexual function,^60^ environmental exposure, cigarette smoking, sleep,^61^ stress,^62^ dietary supplement intake, dietary and alcohol intake,^63^ chrononutrition profile,^64^ physical activity,^65^ sedentary behaviour
Anthropometric and blood pressure measures	Body height, weight, body fat composition (InBody 970, USA), blood pressure
Biochemical tests (blood/urine samples)	HbA1c, lipid profile, cortisol, oxidative stress, inflammatory biomarkers, environmental pollutants (endocrine-disrupting chemicals), exosomes, microbial-derived metabolites
Semen analysis	Semen volume, sperm density, sperm motility, sperm morphology, sperm DNA fragmentation
Molecular analysis	mRNA expressions, sncRNA expression, DNA methylation

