#### Cases

Men aged 21–49 years.Men with a female partner aged 21–39 years.Couples who are not able to conceive for at least 12 months of regular, unprotected intercourse.Couples who are Singapore citizens or permanent residents.

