#### Controls

Men aged 21–49 years.Men with a female partner aged 21–39 years.Men with proven fertility indicated by female partners who are currently pregnant and with viable intrauterine pregnancy at gestational weeks of less than or equal to 16 at the time of the study.Couples with attempted time to conceive within 12 months to achieve this pregnancy.Couples who are Singapore citizens or permanent residents.

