We will include the identified male factors from aim 1, along with female factors which are known to be associated with successful pregnancy in a multivariable logistic regression. The male factors will focus on those easily accessible measurements. The female factors include age, BMI, smoking exposure, dietary habit, alcohol consumption and folic acid supplementation, which we have identified in our previous study.^52^ We will also include some important clinical data and other maternal factors such as the duration of active conception attempts, sexual health issues and probable depression in the logistic regression to further select the predictors. To ensure accuracy, we will use weighted logistic regression, adjusting the model based on the updated prevalence of successful pregnancies within a year in the population to correct for sampling biases. The best-fitting model will be determined using Akaike’s information criteria. Subsequently, we will create a point-based scoring system based on the final model coefficients,^53^ making it easily applicable in community settings. Integer points will be assigned depending on the presence or absence of each factor, allowing the estimation of overall probability by summing the points. Higher point values will indicate higher chances of pregnancy. To facilitate calculation of the fertility index score, all continuous variables will be categorised based on clinical thresholds or appropriate percentiles prior to the analysis. We will repeat the same procedures by including male metabolic biomarkers and semen parameters that are associated with successful pregnancy in the weighted logistic regression. This will enable the generation of various versions of the fertility index, catering to different levels of complexity for application in primary and tertiary care settings.

Subsequently, we will use 10-fold cross-validation to assess the performance of the derived logistic regression models and respective fertility index scores. This cross-validation procedure helps evaluate the model’s performance on different subsets of the data, providing an estimate of its predictive ability and generalisation performance. The fertility index will be evaluated for its discriminatory ability in predicting chances of pregnancy based on the area under the receiver operating characteristic curve (AUROC), with value >0.80 indicating that the model exhibits a good discriminatory ability or predictive value.

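### In controls the past-month exposure window falls largely after conception, yet pregnancy-sensitive female items from it are used to predict pregnancy

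*Protocol article*

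**What the plan says.** Under Data collection and management, the protocol article places all collection at one time: "During the study visit (the only single timepoint visit". Staff gather "self-reported data on behavioural, lifestyle and environmental factor exposures from the past month using standardised questionnaires", and at the same visit "the staff will conduct anthropometric and body fat composition measurements". The window is justified by the instruments, not by the date of conception: "The selection of the recall timeframe is based on the period specified in the validated questionnaires (table 1".

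The two groups reach that visit in different states. The inclusion criteria for controls require "female partners who are currently pregnant and with viable intrauterine pregnancy at gestational weeks of less than or equal to 16" weeks. The criteria for cases require "Couples who are not able to conceive for at least 12 months of regular, unprotected intercourse".

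Table 1 lists the same female items for both groups, including smoking, supplements, diet, alcohol, probable depression, weight and body fat. Under Aim 2 of the Statistical analysis plan, "The female factors include age, BMI, smoking exposure, dietary habit, alcohol consumption and folic acid supplementation", and probable depression is among the further candidates. Aim 1 adjusts for female factors that are related both to the male factors and to successful pregnancy. The article states no preconception reference period and no pre-pregnancy weight. The limitations in the Discussion name recall bias, residual confounding and generalisability, and count short recall periods as a protection.

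**The concern.** A case-control study always asks its questions after the outcome is known, but the exposure period asked about should come before it. Here the article fixes a window that, in controls, mostly follows conception. Women commonly change supplement use, alcohol, smoking and diet once they know they are pregnant, and mood and weight can change as well. An index meant to estimate the chance of pregnancy could then award points for behaviour adopted because of pregnancy.

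The planned safeguards do not reach this problem. Weighting, propensity scores, multiple imputation, interaction tests and stratification all work on the same recorded values. Ten-fold cross-validation would reproduce the distortion in every fold, because training and test couples are measured in the same way. Good internal discrimination would then say little about couples who are still trying to conceive, for whom the index is intended. In Aim 1, adjusting a male factor for a female value that pregnancy has changed is not adjustment for a preconception confounder.

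**Working it through.** The article gives no figure on this point to reproduce. Its sample size is not in dispute: n per group = 2(1.960 + 1.282)² × 4² / 1.3² ≈ 199, against the stated 200, and 400 × 1.2 = 480.

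**1. Timing**

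Inputs from the article: a past-month window, and controls at 16 weeks or less. Assumptions: conception at about gestational week 2 and a window of 30/7 = 4.29 weeks.

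Share of the window after conception = (gestational week − 2) / 4.29, capped at 1.

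- Week 5: 3 / 4.29 = 70%
- Week 6: 4 / 4.29 = 93%
- Week 6.3 and later: 100%
- Week 16: the window opens at 16 − 4.29 = week 11.7

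Over most of the eligible range, the recorded month contains no preconception time.

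**2. One item with no true difference**

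All rates are assumptions; the documents give none. Preconception use of folic acid is p₀ in both groups. Cases report p₀, and controls report the in-pregnancy rate p₁.

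OR = [p₁/(1 − p₁)] / [p₀/(1 − p₀)]; AUROC of the single item = 0.5 + (p₁ − p₀)/2.

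| p₀ (cases) | p₁ (controls) | Spurious OR | AUROC |
|---|---|---|---|
| 70% | 80% | 1.7 | 0.55 |
| 80% | 90% | 2.25 | 0.55 |
| 60% | 90% | 6.0 | 0.65 |
| 40% | 80% | 6.0 | 0.70 |
| 40% | 90% | 13.5 | 0.75 |
| 40% | 95% | 28.5 | 0.775 |

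The case rate matters as much as the rate in pregnancy. If cases have raised their use during a long attempt, the contrast moves towards the top rows.

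**3. Three items together, still with no true difference**

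Assume three independent items with favourable preconception rates of 40%, 60% and 90%. A share s of the remaining control women switch, so p₁ = p₀ + (1 − p₀)s. At s = 0.7 the control rates are 82%, 88% and 97%. The AUROC of the likelihood-ratio score is:

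- s = 0.3: 0.62
- s = 0.5: 0.70
- s = 0.7: 0.78
- s = 0.9: 0.86

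The article treats values above 0.80 as good discrimination. In this illustration the benchmark is approached at 70% switching and passed at 90%.

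**4. BMI**

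For an assumed gain of 1 to 2 kg at a height of 1.60 m, the shift is 1/1.60² to 2/1.60², or 0.39 to 0.78 kg/m². This is small, and it raises BMI in controls.

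**The case against.** The strongest reply is that cases are not an undisturbed baseline either. They enter after at least a year without conception, largely from infertility clinics, and may have changed diet, supplements or mood in response. This stands. The fault is therefore not confined to controls, the net bias could be smaller than a comparison with unchanged cases suggests, and re-dating the control window alone would exchange one difference in measurement for another.

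A second reply is that the validated forms fix their own period and that short recall limits error. That is a real cost of any change, but a short window does not help when it opens after the outcome.

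Third, Aim 1 chooses confounders with directed acyclic graphs, so it is not settled that every listed female item will be an adjuster. This stands too; the firm problem is in Aim 2. The exact wording of the smoking and supplement items is also not shown, and medical-record forms are used for some data. That lowers certainty only slightly, because the past-month rule is stated for behavioural and lifestyle items generally.

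Some stronger readings are tempting but unsupported:

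- A reader might infer that these factors are consequences of pregnancy. The documents show only that they are measured after it and can be changed by it.
- A reader might infer that the AUROC must be inflated and the index must fail. The direction is not established for every item. If higher female BMI lowers fertility, a weight gain in control women would weaken that signal rather than create one.
- A reader might extend the point to male behaviour. A shift in partners is possible, but nothing in the documents shows it.
- A reader might add age at the visit. Pregnancy does not change age, so it is not part of this point.

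**Conclusion.** The concern holds for the pregnancy-sensitive female items in Aim 2, and possibly for the Aim 1 adjustment. It follows from rules that the article itself states, namely the visit, the window, the control definition and the predictor list. An unseen analysis plan cannot recover a preconception exposure that was never asked about.

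The timing conclusion rests only on conception at about week 2 and a 30-day month. The size is uncertain: for folic acid the spurious odds ratio runs from about 1.7 to 28.5 across the assumed rates, and no single value in that range should be relied on. Apparent discrimination could come close to 0.80 with no preconception difference, but whether it would do so depends on how many women switch and on what cases report. The effect is likely to be largest for folic acid, alcohol, smoking, diet and mood, and smaller for BMI.

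**What to change.** - Define a comparable reference month in both groups. For controls, use the month before the last menstrual period. For cases, use a stated month during the attempt to conceive, fixed by the same rule for all of them.
- For control women, calculate BMI from pre-pregnancy or booking weight, not from weight at the study visit.
- Leave out of the index any pregnancy-sensitive item available only as a during-pregnancy value, or report it only in a separate sensitivity analysis. The same applies to couples already enrolled whose answers cannot be dated, since the article describes one visit and no later contact.
- In Aim 1, use as adjusters only female values that refer to the preconception month.
- Add the timing problem, in both groups, to the limitations beside recall bias.

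The cost is a change to questionnaire wording and the extraction of an earlier weight. Recall in controls lengthens by up to about 16 weeks, so that the month asked about ends up to 16 weeks back and begins up to about 20 weeks back (16 + 4.29). The validated forms are then used with a shifted reference month. An earlier month for cases is less affected by the failed attempts but also lengthens their recall, so the choice should be stated with its reason. The sample size does not change.

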**Female partners**	
Sociodemographic, clinical, behavioural, lifestyle and environmental factors	Age, country of origin, length of time in Singapore if born overseas, ethnicity, education, occupation, monthly income, medical history, medication, family history, reproductive health history, female sexual function,^66^ environmental exposure, cigarette smoking, sleep,^61^ probable depression,^67^ dietary supplement intake, dietary and alcohol intake,^63^ chrononutrition profile,^64^ physical activity,^65^ sedentary behaviour
Anthropometric and blood pressure measures	Body height, weight and body fat composition (InBody 970, USA), blood pressure

HbA1c, glycated haemoglobin; sncRNA, small non-coding RNA

### Biosampling and biomarker analyses

Male partners of participating couples will be requested to provide peripheral blood, urine and semen samples during their study visit. The blood samples will be processed and analysed for metabolic and stress biomarkers at the biochemical laboratory of KKH within 1–2 hours. The semen samples will be obtained through masturbation after a period of 2–3 days of sexual abstinence. They will be collected in sterile 50 mL non-spermiotoxic polypropylene containers and allowed to liquefy at room temperature. Once the semen has liquefied, basic semen parameters, including volume, density, motility and morphology, will be evaluated in the semen analysis lab of KKH using the LensHooke X12 Pro Semen Analysis System (X12, Bonraybio, Taiwan), following the criteria established by the WHO.^44^ Single- and double-stranded DNA breaks in sperm will be measured using the sperm chromatin dispersion assay (LensHooke R10 Plus kit) and sperm DNA fragmentation releasing assay (LensHooke R11 Plus kit), respectively.^45^ Oxidative status of blood and seminal plasma will be assessed using the point-of-care NMR system.^46 47^ Additional blood and semen samples will be stored at −80°C for future analyses such as inflammatory biomarkers, environmental chemicals and other related biochemical markers.

### Gene expression and DNA methylation analyses

Blood for gene expression analysis will be collected in either Tempus or PAXgene blood RNA tubes, in which total RNA will be extracted. Sperm samples will undergo purification through centrifugation using PureSperm reagents. To extract sperm RNA, we will use an optimised protocol, adapted from Nätt *et al*.^48^ Disulfide bonds will be broken using metal beads and β-mercaptoethanol before RNA extraction using the mirVana RNA isolation kit. Reverse transcription-quantitative real-time PCR will be conducted using the real-time PCR system (Life Technologies, Thermo Fisher Scientific). To determine the fold-change in mRNA expression (normalised against a housekeeping gene GADPH) for a particular participant, we will employ the 2^−ΔΔCt^ method. Additionally, to compare mRNA expression differences between groups, we will use the standard curve method to determine the exact copy amount of RNA.

In addition to mRNAs, we will also characterise the small non-coding RNAs (sncRNAs) and DNA methylation landscapes of human sperm to explore their expression and methylation profiles in relation to paternal modifiable factors and pregnancy status. sncRNAs and DNA methylation have been demonstrated to be regulated by paternal exposures and were suggested to be associated with sperm functionality and embryo development.^4049^,^51^ Genome-wide bisulfite sequencing (to profile global DNA methylation) for sperm from cases and controls will be performed as previously described.^49^ Briefly, genomic DNA from sperm cells will be extracted and treated with bisulfite using the EZ DNA Methylation Lightening Kit (Zymo Research) in accordance with the manufacturer’s protocol. The samples were further subjected to PCR amplification and sequencing using the Illumina platform. Top differentially methylated genes will be selected based on their known functions in spermatogenesis, fertility and metabolic pathways such as insulin signalling, and further verified by targeted bisulfite sequencing using the remaining sperm samples from the cohort.

### Statistical analysis plan

#### Aim 1

We will use multivariable logistic regression model to assess the association between case versus control status and male factors, adjusting for potential confounders such as male sociodemographics, general health, as well as female factors which are correlated with both male factors and successful pregnancy. We will identify these potential confounders through a literature review and conceptual framework, guided by directed acyclic graphs. We will explore propensity score methods, such as inverse probability weighting, to ensure balanced distribution of confounders across case and control groups. We will use the least absolute shrinkage and selection operator regression to select male factors for inclusion in the final model.

#### Aim 2

We will include the identified male factors from aim 1, along with female factors which are known to be associated with successful pregnancy in a multivariable logistic regression. The male factors will focus on those easily accessible measurements. The female factors include age, BMI, smoking exposure, dietary habit, alcohol consumption and folic acid supplementation, which we have identified in our previous study.^52^ We will also include some important clinical data and other maternal factors such as the duration of active conception attempts, sexual health issues and probable depression in the logistic regression to further select the predictors. To ensure accuracy, we will use weighted logistic regression, adjusting the model based on the updated prevalence of successful pregnancies within a year in the population to correct for sampling biases. The best-fitting model will be determined using Akaike’s information criteria. Subsequently, we will create a point-based scoring system based on the final model coefficients,^53^ making it easily applicable in community settings. Integer points will be assigned depending on the presence or absence of each factor, allowing the estimation of overall probability by summing the points. Higher point values will indicate higher chances of pregnancy. To facilitate calculation of the fertility index score, all continuous variables will be categorised based on clinical thresholds or appropriate percentiles prior to the analysis. We will repeat the same procedures by including male metabolic biomarkers and semen parameters that are associated with successful pregnancy in the weighted logistic regression. This will enable the generation of various versions of the fertility index, catering to different levels of complexity for application in primary and tertiary care settings.

Subsequently, we will use 10-fold cross-validation to assess the performance of the derived logistic regression models and respective fertility index scores. This cross-validation procedure helps evaluate the model’s performance on different subsets of the data, providing an estimate of its predictive ability and generalisation performance. The fertility index will be evaluated for its discriminatory ability in predicting chances of pregnancy based on the area under the receiver operating characteristic curve (AUROC), with value >0.80 indicating that the model exhibits a good discriminatory ability or predictive value.

Given that the fertility index comprises male and female factors, we will perform additional analyses to evaluate the individual performance of the index that includes only male factors or female factors using the AUROC. We will also evaluate the performance of the male factor index, with adjustment of female factor index.

#### Aim 3

We will use multivariable linear regression to examine the association between modifiable factors and semen parameters, adjusting for sociodemographic factors.

To understand the relationships between male factors and fertility indices across different conception methods, we will replicate the above analyses by examining outcomes based on assisted and unassisted conception. To assess potential selection bias in both studies, we will compare baseline characteristics between participants with and without a complete set of data. We will use multiple imputation by chained equation to handle missing values.^54^ Sensitivity analyses will be conducted using only samples with complete data. To further ensure robustness, we will test interactions between male and female factors and stratify analyses by key confounders. Statistical analyses will be conducted using the Stata Statistical Software.

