**Methods and analysis:**

We will conduct an unmatched case-control study involving 240 couples with impaired male fertility (cases) and 240 couples with normal male fertility (controls). Between July 2024 and June 2026, we will recruit 480 eligible couples from KK Women’s and Children’s Hospital, Singapore. Male and female participants will complete questionnaires on sociodemographics, general health and lifestyle factors, and their anthropometry and body fat composition will be measured. Blood and semen samples from the male participants will be collected for biochemical, molecular and semen analyses. Predictive male factors will be identified using the least absolute shrinkage and selection operator method, accounting for female factors. We will construct a logistic regression model incorporating both male and female factors to derive a fertility index, which will be evaluated using cross-validation on subsets of the study population. Multivariable linear regression will be used to explore relationships between male modifiable exposures and semen parameters.

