### Objectives

The overall objective of this study is to determine the contribution of male factors to successful pregnancy after accounting for female factors and gain a deeper understanding of the biological mechanisms that underlie this relationship. Specifically, we aim to:

Identify male factors associated with the likelihood of pregnancy, independent of female factors.Develop a fertility index that integrates modifiable factors for both males and females to estimate the likelihood of pregnancy.Explore the relationships between male modifiable factors, oxidative status, sperm physical and molecular characteristics.

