### Sample size

There is no straightforward, universally accepted method to estimate the required number of participants for developing a multivariable prediction model. Thus, we employed a few alternative methods to estimate the sample size required. We used paternal BMI as an indicator reflective of paternal lifestyle and metabolic factors that are associated with successful pregnancy and expect that it may be retained in the prediction model. Based on the assumption that males with impaired fertility will have an average BMI 1.3 unit higher than the fertile males,^55 56^ and considering a BMI SD of 4 kg/m^2^, a two-sided 5% type 1 error rate and a power of 90%, the minimum required sample size to detect a difference in BMI between cases and controls is 400 couples (200 cases:200 controls). Considering a variance inflation factor of 1.2 for adjustment of maternal factors and other covariates, the study will need to recruit 480 couples (240 cases:240 controls).

Previous studies have reported the use of the event per variable (EPV) ratio:the number of events (success pregnancy) divided by the number of regression coefficients in the model to determine the sample size of a multivariable model.^57^ An EPV of at least 10 has been recommended to avoid overfitting.^58^ We estimate 15 regression coefficients based on the independent male predicting factors of successful pregnancy in the logistic model. Following this guideline, we require 150 events. Given the observed pregnancy rate of 48% in the population,^59^ the total sample size calculated to achieve this number of events is approximately 313 (150/0.48). By accounting for a variance inflation rate of 1.2 for correlation between male and female factors, we will require 376 couples (188 cases:188 controls) in the study.

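### Aim 1 selects male factors by LASSO and estimates their associations in the same couples with no stated correction, so intervals for null or weak factors that survive selection are likely to be too narrow

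*Protocol article*

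**What the plan says.** The first objective is an association question: "Identify male factors associated with the likelihood of pregnancy, independent of female factors" (Protocol article, Objectives). The Aim 1 text of the Statistical analysis plan opens with the tool for it: "We will use multivariable logistic regression model to assess the association between case versus control status and male factors", adjusted for confounders chosen with the help of directed acyclic graphs (DAGs). It ends with the selection step: "We will use the least absolute shrinkage and selection operator regression to select male factors for inclusion in the final model". The Abstract describes the same step: "Predictive male factors will be identified using the least absolute shrinkage and selection operator method, accounting for female factors".

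The only internal validation is under Aim 2: "we will use 10-fold cross-validation to assess the performance of the derived logistic regression models and respective fertility index scores". The closing paragraph of the analysis plan adds complete-case, interaction and stratified analyses. The propensity score methods in Aim 1 are meant to balance confounders. None of these deals with the effect of selection on the Aim 1 estimates. No sample split, post-selection method, double selection or bootstrap of the selection step is stated.

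**The concern.** A factor that LASSO retains has, by construction, looked associated with case status in these couples. If the same couples then supply its odds ratio and a standard 95% interval, the interval treats the factor as though it had been named in advance. For a factor with no effect, or a weak one, survival depends partly on a favourable chance fluctuation, and the interval carries that fluctuation without allowing for it.

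Cross-validating the Aim 2 models, however carefully, concerns their predictive performance. It leaves the Aim 1 odds ratios and intervals unchanged.

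At stake is the list of male factors that the study will name under its first objective. The candidate pool in Table 1 is broad, spanning lifestyle, environmental, body composition, biochemical, semen and molecular measures. The Sample size section expects only 15 male coefficients. A reader of the results would take an interval excluding 1 at face value.

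**Working it through.** **1. The plan's own figure.** The Sample size section assumes that "males with impaired fertility will have an average BMI 1.3 unit higher than the fertile males", with SD 4 kg/m², two-sided 5% error and 90% power.

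n per group = 2 × (z₀.₉₇₅ + z₀.₉₀)² × SD² / Δ² = 2 × (1.960 + 1.282)² × 16 / 1.69 ≈ 199

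The plan states 200, and 200 × 1.2 = 240 per group. The sample size reproduces and is not at issue. It fixes the 240:240 used below.

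**2. Assumed inputs.** The article gives no number of candidates, correlations, true effects or penalty rule. All simulations use 240 cases, 240 controls and a cross-validated logistic LASSO, followed by an unpenalised logistic refit on the same data with standard 95% intervals. The correlation between candidates is 0.2. Confounder adjustment, weighting and imputation are not modelled.

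**3. Set A.** 400 replicates per scenario, 10-fold cross-validation, each true effect a log odds ratio of 0.25 per SD.

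| Candidates (true effects) | Mean retained | Null factors retained | Retained nulls with p<0.05 | Coverage, all retained | Coverage, retained true effects | Mean estimate, true effects |
|---|---|---|---|---|---|---|
| 15 (3) | 6.3 | 3.51 | 17.0% | 89.3% | 97.1% | 0.248 |
| 30 (5) | 11.3 | 6.67 | 17.1% | 89.1% | 97.9% | 0.242 |
| 50 (5) | 13.4 | 8.92 | 18.1% | 87.1% | 97.5% | 0.237 |

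Comparator without selection (all candidates in one logistic model; range over these and the no-effect scenarios): 5.4% to 6.2% of null factors have p<0.05, and coverage is 93.7% to 94.6%. The shortfall in the table therefore comes from selection and not from the sample size.

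Extreme case with no true effects at all: 42% to 50% of retained nulls have p<0.05, and coverage is 50% to 58%.

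**4. Set B.** Four true effects (log odds ratios 0.325, 0.2, 0.1 and 0.1 per SD), 5-fold cross-validation.
- 30 candidates (200 studies): 21% of retained nulls have p<0.05.
- 60 candidates (150 studies): 27%.
- A repeat with separate code gave 20% (150 studies) and 23% (80 studies), with coverage over retained factors of 85% at 30 candidates.

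**5. Set C.** 15, 30 and 60 candidates: 16%, 20% and 22% of retained nulls have p<0.05. Coverage over retained factors is 90%, 86% and 82%.

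**6. False-positive rate per candidate, counting dropped factors as non-significant.** From set A, this is nulls retained × share with p<0.05 ÷ number of null candidates:
- 3.51 × 0.170 / 12 = 5.0%
- 6.67 × 0.171 / 25 = 4.6%
- 8.92 × 0.181 / 45 = 3.6%

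Set B gives 3% to 4% and set C 2% to 4%. None exceeds the nominal 5%. The fault lies in the intervals conditional on retention and not in the overall rate of false claims per candidate.

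**The case against.** **The refit is not written out.** The article mentions no refit, interval, p value or significance rule for Aim 1. It is a condensed account, and the full analysis plan could name a valid post-selection method. This stands as a limit on certainty. It does not remove the point, because the article itself prescribes data-driven selection of the terms in a model that serves an association aim.

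**Another reading is possible.** The associations might come from the DAG-adjusted model named at the start of Aim 1, with LASSO serving only to pass predictors to Aim 2. If so, a sentence saying this would settle most of the matter. But the Abstract says that LASSO identifies the factors, and Aim 1 ends with LASSO defining its final model, so the text does not make that reading clear.

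**Stronger claims a reader might infer.** Four go too far.
- *LASSO makes spurious findings more common.* In set C, at least one null factor reached p<0.05 in 35%, 38% and 58% of studies with LASSO and refit, against 38%, 70% and 98% with no selection. That share mostly reflects testing many factors without adjustment.
- *LASSO inflates weak effects in a special way.* In set B, log odds ratios of 0.10 averaged about 0.16 when retained. In the same setting with no selection, those that reached p<0.05 averaged 0.27. The two filters differ, but the comparison shows that low power behind any filter inflates weak effects.
- *All retained intervals are wrong.* Retained true effects of 0.25 kept 97% to 98% coverage.
- *Coverage falls to 50%.* That requires no male factor to have any effect, which the documents give no reason to assume.

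**Conclusion.** The point holds in a limited form. Aim 1 as stated chooses and estimates on the same couples and names no correction. Read as a logistic refit with standard intervals, it gives null or weak factors that survive selection intervals that are too narrow. Under the assumed inputs (15 to 60 candidates, correlation 0.2, a few modest true effects), about 16% to 27% of retained null factors have p<0.05, and coverage over retained factors is about 82% to 90%. The size moves with the number of candidates, the penalty rule and the true effects, none of which the article gives. Retained moderate true effects are little affected. The plan should be changed, but the design, recruitment and sample size need no change on this account.

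**What to change.** - Prespecify the list of male factors whose associations Aim 1 will report.
- Take their odds ratios and intervals from a model in which plain LASSO chooses neither the factor of interest nor the DAG confounders. The prespecified DAG-adjusted logistic model will do. If candidates are many, use double-selection or cross-fit partialling-out LASSO logistic regression.
- Use plain LASSO only to choose predictors for Aim 2. Label any factor found only through LASSO as exploratory and report its bootstrap selection frequency.
- State in Aim 1 which model supplies the reported estimates.

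Multiplicity adjustment across the list is a separate, optional matter and does not repair post-selection coverage.

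The cost is more analysis work, which can be done in the Stata software already planned, together with somewhat wider intervals and fewer factors called significant. No further couples or measurements are needed.
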